### Ethical considerations

We discussed all ethical issues with the Institutional Review Board of Shiraz University of Medical Sciences, which ultimately approved the study protocol (IR.SUMS.REC.1400.409). Informed consent will be obtained once patients are clinically stable and sedatives or strong analgesics do not alter their consciousness. Importantly, the use of low balloon inflation pressure and divided (three-part) infusions will prevent complications related to intracoronary cell infusion. The principles of the *Declaration of Helsinki* will be upheld throughout this study.

## Discussion

Currently, the primary focus of post-AMI treatment is to prevent remodeling and avert any further loss of myocytes [5]. However, a revolution can potentially be achieved by regenerative medicine, aiming to restore cardiac function by inhibiting and even reversing the process of remodeling through the use of stem cells [24]. Even though some investigations were not very promising in this regard [8], other studies have shown that stem cell therapy may be of value in certain populations.

Although a Cochrane meta-analysis revealed that the LVEF of young AMI patients does not increase following BM-MNC therapy, survival and functional benefits may be present [23]. Importantly, research with MSCs has yielded more promising results, with the TAC-HFT trial indicating the roughly twofold higher efficacy of MSCs relative to BM-MNCs [19]. According to meta-analyses of the various clinical trials, MSCs can improve the LVEF by 5.72% [25], while BM-MNCs can achieve an inferior improvement of 3.07% [26].

Currently, scientists are yet to understand the exact mechanisms behind the therapeutic impact of stem cells, especially MSCs. However, the most commonly suggested mechanism is paracrine signaling, where the implanted stem cells alter the activity of the nearby cells in the heart via mediators like cytokines [28]. Also, it is still unclear whether or not the mechanical improvements in LV function after MSC transplantation would be translated into a clinical benefit by reducing major cardiovascular events. Our trial provides essential insights into the field by including selected patients who develop reduced LVEFs after AMIs.

Our trial, enrolling 390 patients, would be the largest clinical trial ever conducted in the field of regenerative medicine on myocardial infarction. We hope it would help clarify whether MSC transplantation is clinically useful or not.

### Trial status

We began enrolling patients in Jan 2021 and expect to finish the recruitment process by Nov 2022. Data will be collected until Nov 2024. Thereafter, the analysis will be conducted. Results are expected to be ready by Dec 2024. We will prepare and submit the related manuscript following the CONSORT guidelines. This study is registered with *ClinicalTrials.gov* under the code NCT05043610. This protocol (version 1) was approved in Oct 2020. Changes in protocol will be submitted to the registration site.

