**Methods:**

This single-blinded, randomized, multicenter trial aims to establish whether the intracoronary infusion of umbilical cord-derived Wharton’s jelly MSCs (WJ-MSCs) helps prevent HF development after AMI. The study will enroll 390 patients 3 to 7 days following AMI. Only patients aged below 65 years with impaired LV function (LVEF < 40%) will be included. They will be randomized (2:1 ratio) to either receive standard care or a single intracoronary infusion of 10^7^ WJ-MSCs. The primary outcome of this study is the assessment of HF development during long-term follow-up (3 years).

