### Sample size

Since the primary outcome of this study is to compare the incidence of HF and considering the one-year incidence rate of 1.3% and 4% in the BAMI trial [3], it is predicted that in a 3-year period follow-up of considered for the present study, the incidence rate of this indicator will be 3.9% and 12% in intervention and control groups respectively. According to the formula $$\boldsymbol{n}=\frac{\frac{\mathbf{1}+\boldsymbol{R}}{\boldsymbol{R}}\overline{\ \boldsymbol{P}}\Big(\mathbf{1}-\overline{\boldsymbol{P}\Big)}{\left({\boldsymbol{t}}_{\boldsymbol{\alpha}, \boldsymbol{\nu}}+{\boldsymbol{t}}_{\boldsymbol{\beta} \left(\mathbf{1}\right),\boldsymbol{\nu}}\right)}^{\mathbf{2}}}{{\left(\boldsymbol{\partial}\right)}^{\mathbf{2}}}$$, and the enrolment ratio of 2:1 in case and control groups, and considering the first type error of 5% and the power of 80%, the required sample size is approximately 220 people in control and 118 people in case group***s***, which makes a total of 328 people. To increase the accuracy of sampling and the possibility of using regression models, the sample size was increased to 390 people. The sample size is approximate and the above formula is summarized. In the above formula $$\overline{P}$$, the weighted average of the values in the two groups is used, and the *t* values are equal to the 0.8 and 0.975 percentiles of the standard normal distribution and equal to 1.96 and 84. The denominator of the fraction (∂) is the difference of two amounts. R is the ratio of two groups, which is 2 here.

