### Follow-up and endpoints

Patients will receive daily visits from a cardiologist during hospitalization. The results of all physical examinations will be recorded, and patients will be monitored for early manifestations signaling arrhythmia, pulmonary embolism, or coronary artery injury. Blood tests will be done to measure fasting blood sugar, complete blood count, C-reactive protein, urea and electrolytes, liver function test, creatine kinase, and cardiac troponin T. An electrocardiogram (ECG) will also be obtained. Prior to the MSC infusion process, the cardiac evaluation will be completed using echocardiography. The initial EF will be established according to the wall motion score and Simpson’s rule. After the MSCs are delivered, once stable, a beta-blocker, angiotensin-converting enzyme (ACE) inhibitor, aldosterone antagonist, aspirin, ticagrelor, statin, and glyceryl trinitrate (spray or tablets) will be prescribed for the patient to use at home. A cardiac rehabilitation program will also be completed. Subsequent visits will be at ten days after discharge and then every three months when an ECG and blood tests will be requested. Echocardiography will be done during the six-month follow-up and the final visit, facilitating the evaluation of LV systolic function.

Our primary endpoint to assess the efficacy of the intervention will be the incidence of HF. Secondary endpoints include the improvement in LV function (through calculation of LVEF) after six months and after three years alongside echocardiographic changes in the left ventricular mass, left ventricular end-diastolic volume, left ventricular end-systolic diameter, and global longitudinal strain (measured via automated formulas in standard views) indices.

Data will be entered, encoded, became secure, and stored in a local database.

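### The stated calendar cannot give three years of follow-up to patients enrolled after about Nov 2021, which contradicts the three-year primary outcome, the sample-size rates and the three-year echo endpoint

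*Protocol article*

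**What the plan says.** All references are to the protocol article.

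- **Trial status** gives the calendar: "We began enrolling patients in Jan 2021 and expect to finish the recruitment process by Nov 2022. Data will be collected until Nov 2024". It then adds: "Results are expected to be ready by Dec 2024". The Discussion paragraph of the Abstract repeats the closing and results dates.
- **Abstract, Methods** sets the time frame of the primary outcome: "The primary outcome of this study is the assessment of HF development during long-term follow-up (3 years").
- **Sample size** starts from annual figures, "considering the one-year incidence rate of 1.3% and 4% in the BAMI trial", and triples them for a three-year period, so that "the incidence rate of this indicator will be 3.9% and 12% in intervention and control groups respectively".
- **Follow-up and endpoints** lists as secondary "the improvement in LV function (through calculation of LVEF) after six months and after three years", together with other echocardiographic indices. Visits are three-monthly after the first post-discharge visit. Echocardiography is done at six months and at the final visit.
- **Statistical analysis** compares heart failure incidence by Cox regression and EF by an independent t-test.

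The article mentions no minimum follow-up below three years, no common closing date with variable follow-up, and no data collection after Nov 2024.

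**The concern.** Enrolment ends in Nov 2022 and data collection ends 24 months later. Three years of observation per patient is therefore impossible for everyone enrolled in roughly the last year of recruitment. This is not a detail that an analysis plan could supply, because no analysis plan can create follow-up after data collection has closed.

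Two things are at stake:

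1. **The late echo endpoint.** It is tied to a final visit. For later enrollees that visit falls somewhere between about two and three years. Either those patients have no three-year value, or values taken at different times are pooled and reported as three-year results. A t-test has no censoring mechanism to absorb this.
2. **The primary time frame and the power statement.** The sample size assumes that every patient is observed for the full three years. If that is not so, fewer events are expected. It is also unclear whether patients are censored at 36 months or at the closing date. Leaving that choice open until data have accrued is undesirable in a trial where only the outcome assessors are blinded.

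**Working it through.** **Inputs.** Enrolment Jan 2021 to Nov 2022, data to Nov 2024 (Trial status). Three-year incidences 3.9% and 12%, N = 390, 5% type I error, 80% power (Sample size); two-sided tests (Statistical analysis). Intervention arm 130 (Intervention). I take 260 controls, from 390 − 130 and the 2:1 ratio. Uniform accrual is my assumption.

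**The plan's own figure.** The stated formula is n = [(1+R)/R]·P̄(1−P̄)·(1.96+0.84)²/∂², with R = 2 and ∂ = 0.12 − 0.039 = 0.081. With P̄ = 0.066:

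n = 1.5 × 0.066 × 0.934 × 7.84 / 0.006561 = 110.5, 2n = 221, total 331.5.

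This is close to the stated 328, so the calculation does use full three-year incidences. (The stated groups, 220 and 118, add to 338, and P̄ = 0.066 gives the intervention rate two-thirds of the weight although the control group is the larger. Those are separate matters.)

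**Who can reach 36 months.** Nov 2024 minus 36 months is Nov 2021. Enrolment lasts about 22 months, of which about 10 precede that date.

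- Share falling short: 12/22 = 54.5%, and 0.545 × 390 ≈ 213 patients.
- Varying the day within each stated month: 50.2% to 59.0%, or about 196 to 230 patients.
- Follow-up available: about 1.9 to 2.1 years for the last patient and 3.75 to 3.9 years for the first.

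**Mean follow-up.**

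- Capped at 36 months: (10/22) × 36 + (12/22) × 30 = 32.7 months.
- Not capped (everyone followed to Nov 2024): (24 + 46)/2 = 35 months.

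**Expected heart failure events** (incidence proportional to time, as the plan's tripling implies).

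- Full three years: 130 × 0.039 + 260 × 0.12 = 5.07 + 31.2 = 36.3.
- Capped: 36.3 × 32.7/36 = 33.0.
- Not capped: 36.3 × 35/36 = 35.3.

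**Power** (130 and 260 patients, two-sided 5%). The Schoenfeld figure is Φ(|ln HR|·√(D × 1/3 × 2/3) − 1.96), where D is the number of events and HR = ln(1 − 0.039)/ln(1 − 0.12) = 0.311. The two-proportion figure is the usual normal approximation, with incidences of 3.9% and 12% (full) or 3.5% and 10.9% (capped). The simulations use exponential hazards that give 3.9% and 12% at three years.

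| Method | Full 3 years | Capped at 36 months | Not capped |
|---|---|---|---|
| Events | 36.3 | 33.0 | 35.3 |
| Two proportions | 77.4% | 72.5% | 76.0% |
| Schoenfeld | 91.2% | 88.5% | 90.5% |
| Log-rank, simulated | 80% | 75% | 78% |

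The losses run from 0.7 points (Schoenfeld, 91.2 − 90.5) to about 5 points (log-rank, 80 − 75). A simulated Cox Wald test in the capped case falls from about 77% to 71–72%, slightly more. The absolute level depends heavily on the method, but the drop is small by all of them.

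**The case against.** The dates cannot be argued away, but much can be said against reading too much into them.

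- **The primary comparison is by Cox regression.** Every patient contributes until the cut-off, and closing the database on a fixed date is ordinary administrative censoring. A reader might infer that the primary result would be invalid, or would rest only on the minority with complete follow-up. The document does not support that: even with a 36-month cap, 32.7/36 = 91% of the planned person-time is kept. This objection stands.
- **No cap is stated.** If early enrollees are followed to Nov 2024, expected events fall only from about 36 to 35. This stands, and is why the loss is given as a range.
- **A reader might take the guaranteed 24 months as the whole follow-up.** That would give about 25 events and 52% to 61% power. Nothing in the article truncates everyone at 24 months, and doing so would discard collected data. It is not a consequence of this plan.
- **A majority falling short is not established by the dates alone.** The share rests on uniform accrual; front-loaded recruitment could bring it below half and slow early recruitment would raise it. This stands.
- **N was raised from 328 to 390.** Since 390 × 0.91 ≈ 354 exceeds 328, the margin might seem to cover the loss. This stands only in part, because the increase was made for another stated purpose and the 328 is itself open to question.
- **The only numerical EF criterion in Statistical analysis is at six months,** which every patient can reach. This stands and confines the EF problem to the late echo.

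What remains is that four sections of one article cannot all be carried out as written.

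**Conclusion.** The inconsistency is real and follows from the stated dates alone: patients enrolled after about Nov 2021 cannot have three years of follow-up, and the last has about two. Its size, about 55% of patients (50% to 59%), holds under uniform accrual only.

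The late echo comparison is hit hardest, since the final-visit value for all the patients who fall short would come at roughly two to three years or be absent at three. The effect on the primary endpoint is modest: about 33 to 35 events instead of 36, and about 1 to 5 points of power, assuming 130 and 260 patients and the plan's own incidences. The case for correction therefore rests on a time frame and a secondary endpoint that the calendar cannot deliver. It does not rest on a collapse of power or on a biased primary analysis.

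**What to change.** Reconcile Trial status with the Abstract, Sample size, and Follow-up and endpoints. There are two workable routes:

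1. **Extend data collection to about Nov 2025,** 36 months after planned last enrolment, and move the results date to match. The cost is up to 12 more months of the three-monthly visits already scheduled, for later enrollees only, and later results. The endpoints and the sample-size rationale keep their three-year basis.
2. **Keep Nov 2024.** Restate the primary as time to first heart failure event with a common closing date and a minimum of about 24 months' follow-up, and say whether follow-up beyond 36 months counts. Set the late echocardiogram at one time point that every patient can reach. Restate the expected events and power. The cost is a change of wording, slightly lower stated power and the loss of a true three-year EF comparison.

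Either route should be settled and recorded before any unblinded look at the data. The article states that changes to the protocol go to the registration site, so this one should too.

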## Data Availability

Data will be made available upon reasonable request following the completion of the study.

## Abbreviations

AMI: Acute myocardial infarction
BM: Bone marrow
BM-MNCs: Bone marrow-derived mononuclear cells
DSMB: Data and Safety and Monitoring Board
EF: Ejection fraction
HF: Heart failure
LVEF: Left ventricular ejection fraction
MACEs: Major adverse cardiac events
MCSs: Mesenchymal stem cells
MI: Myocardial infarction
SAEs: Serious adverse events
WJ-MSCs: Wharton’s jelly mesenchymal stem cells
